## Abstract

**Background:**

In Germany, approximately three million children under the age of eighteen have a mentally ill parent. These children are at an increased risk of developing a mental illness themselves (1) as well as a physical illness (2). While research has identified numerous evidence-based family-oriented interventions, little is known about how to implement such interventions effectively and efficiently in clinical practice in Germany. This implementation study (ci-chimps) evaluates three clinical implementation projects with three different implementation interventions for the optimal implementation of the tailored family-oriented preventive and therapeutic interventions in the CHIMPS-NET (children of mentally ill parents—research network) with an implementation model for children of mentally ill parents.

**Methods:**

A two-group randomized controlled multicenter trial will examine changes in family-oriented practice and aspects of implementation at baseline as well as at 12- and 24-months follow-up. The CHIMPS-Network consists of 20 clinical centers. The centers in the intervention group receive the support of all of the three implementation interventions: (1) optimal pathways to care, (2) education and a training program for professionals, and (3) systematic screening for children. The centers in the control group do not receive this specific implementation support.

**Discussion:**

While we know that children of mentally ill parents are an important target group to be addressed by preventive and therapeutic interventions, there is often a lack of structured implementation of family-oriented interventions in clinical practice in Germany. Using a randomized controlled multicenter trial design with a large and wide-ranging sample (clinics for adult psychiatry and clinics for child and adolescent psychiatry, university clinics and clinics at the real health care) will provide a robust understanding of implementing family-oriented changes in German clinical practice.

**Trial Registration:**

The CHIMPS-NET-study was registered with the German Clinical Trials Register on 2019-12-19 (DRKS00020380) and with Clinical Trials on 2020-4-30 (NCT04369625), the ci-chimps-study was registered with the German Clinical Trials Register (DRKS00026217) on 2021-08-27, the Clinical Trials registration is in review process.

## Background

In Germany, approximately three million children under the age of 18 have a mentally ill parent (1). These children are at an increased risk of developing a mental illness themselves (1) as well as a physical illness (2). Not all children will be impacted in the same way, and children's outcomes vary depending on the severity and chronicity of the parents' illness, the support provided to the family, environmental factors (such as poverty and housing) and the timing of the illness in relation to the child's age (references see below) (1). To mitigate mental symptoms and concomitant diseases in these children and adolescents, Wiegand-Grefe et al. developed a low-frequency family-oriented intervention for children of mentally ill parents: CHIMPS (3). The term CHIMPS stands for “Children of mentally ill parents.” The acronym CHIMPS might be considered stigmatizing however we have used it positively by employing a chimpanzee as our project mascot. We argue that this makes the acronym fun and playful and thus engaging to children. The CHIMPS intervention has been manualized (3) and evaluated in waiting-list-controlled pilot studies (4–7), which indicates improvements in the mental health of the children (4), the health-related quality of life and social support of children and their families (5), the family functioning (6) and congruent and successful parental coping strategies (7). Furthermore, in the next step, this CHIMPS intervention program has been evaluated in a BMBF funded, multicenter trial (8).

In the current “Children of mentally ill parents-research network” (CHIMPS-NET), funded by the innovation fund at the GB-A, the CHIMPS intervention where updated and more adapted to the heterogeneous needs of each family. In CHIMPS-NET, in a stepped care model, every family with a mentally ill parent and with children from age 3–18 years is screened regarding his/her family functioning and the mental health state of his/her children and adolescents and the parents and allocated to different interventions according to his/her indication and the requirements. For further information about the different family-oriented preventive and therapeutic interventions in CHIMPS-NET, for the design of the evaluation studies, as well for the inclusion and exclusion criteria to each intervention see the study protocol of the central project CHIMPS-NET (9). This publication focused the implementation interventions and the design of the overarching implementation study ci-chimps.

### Implementation Research for Interventions for Children of Mentally Ill Parents

Because of the knowledge and the increasing awareness that children of mentally ill parents are an important target group to be addressed by preventive interventions, there are numerous programs and tools (10, 11). But there is often a lack of structured implementation of family-oriented interventions in clinical practice not only in Germany (10–13). Implementation can be defined as a specified set of activities designed to put into practice an activity or program of known dimensions (14). Lauritzen et al. describe three general implementation categories: “paper implementation,” “process implementation,” and “performance implementation” (13). Paper implementation puts new policies and procedures into place but does not change practice in itself. Process implementation incorporates new procedures into an organization, and performance implementation provides content and tools to practitioners, so that new procedures and processes have functional components for change. Ci-chimps belongs to the performance implementations by giving the clinical centers new tools like the screening (15).

Personal attitudes like self-reported skills and knowledge, beliefs about job role, and perceptions of workplace support seem to have a notable impact in supporting a successful and sustainable implementation (11, 16–20). Furthermore, organizational factors, such as reporting systems, meeting structures, leadership and supervision, are closely associated with satisfaction with the implementation process (11, 17, 19–21).

For family-oriented practice, the following barriers are reported: organizational barriers [policies, leadership and management (22–24)], high workload (22–24), patient-oriented treatment (24), no routines in identifying affected families (21–23), and gaps in mental health professionals' knowledge, and skills about children of mentally ill parents (21–23).

Gregg et al. summarized in their review factors influencing family-oriented practice in a detailed overall diagram with two main parts: Practitioner factors and workplace factors. They subclassify practitioner factors in personal attitudes like beliefs about family-oriented practice and professional subfactors like training and education, job role, skills and knowledge. Workplace factors were subclassified in service-related subfactors e.g., available resources and work setting and support-related subfactors like workplace support and time and workload (11).

Maybery and Reupert are providing an overview of the barriers regarding family-oriented practice. They have designed a model based on a hierarchy with the main factors “organizational policies and procedures (including managerial support),” “workers attitude, knowledge and skills,” and “barriers families themselves bring in” (22). Lauritzen and Reedtz adapted this model for Norway and added the two factors “organization of mental health care services” and “geographical conditions” (13). These papers present the international state of knowledge of the implementation of interventions especially for this target group of children of mentally ill parents.

### The Implementation Model of the CHIMPS-NET Consortium

The implementation science showed that evidence-based interventions will not be effective if not properly implemented (19). In order to achieve a successful implementation, all CHIMPS interventions are based on the Australian model by Maybery and Reupert (22) and the Norwegian model by Lauritzen and Reedtz (13). The CHIMPS-NET consortium specifies the content of prevention and care according to the German healthcare system setting, including adult psychiatry and child and adolescent psychiatry, and develops an own implementation process based on three implementation interventions. Figure 1 shows the three subprojects (SP) for implementing and realizing the hierarchical components of an evidence-based implementation process including the following subprojects: “optimal pathways to prevention and care” [SP1], “improved institutional anchoring and professionals' attitudes, knowledge and skills” [SP2], “systematic screening, early detection, and family engagement” [SP3]. This systematical implementation process is developed to improve the implementation of prevention [SP4a] and therapy [SP4b].” SP5 realizes the online intervention i-chimps, and [SPs 6–8] realizes the medical, health economic, and qualitative evaluation [SPs 6–8]. In summary, ci-chimps realizes an overarching multicenter study to evaluate the implementation process with three implementation interventions [SP 1–3].

**Figure 1 F1:**
[figure not shown]
The CHIMPS-NET Implementation Model [based on (22) and first published (25)] for the health care for children and their mentally ill parents.

Ci-chimps also includes multiple interfaces with general medicine/primary care, pediatrics, youth healthcare services, and public sector services catering for the educational and residential needs of children. In the CHIMPS-NET model, the implementation of CHIMPS-P and CHIMPS-T in the model regions will be well-prepared through interventions at the interfaces, and in this way placed into an environment where experts from psychiatry and psychotherapy for children, adolescents, and adults as well as youth welfare and the civil sector are sensitized for the special requirements of those families. This implementation comprises all aspects of interdisciplinary and intersectional implementation, specific psychosocial intervention for children of parents with mental illness, quality assurance, cost-effectiveness, sustainability, and transfer.

### The Three Implementation Interventions in CHIMPS-NET

The main aim of ci-chimps is the evaluation of the effect of the three implementation interventions in CHIMPS-NET. Referring to this hierarchy, we deduce our three implementation interventions 1) optimal pathways to care, 2) education and training program for the professionals, and 3) systematic screening. To examine the utility of the supported implementation of CHIMPS-NET, a controlled trial design is used. With these three implementation interventions, we want to support the clinical implementation of the family-oriented interventions in CHIMPS-NET.

1) **Optimal pathways to care**

The first implementation measure focuses on optimal ways of caring for mentally ill patients who are also parents with children living in the household. The main goals of this intervention are the specific information of the referring physician, the indicated referral of mentally ill parents, and the consideration of underage children living in the household of the inpatient referral. The two main components are the evaluation of the attitudes of the medical and psychotherapeutic referrers toward the target group, and the intervention as well as the development and implementation of an optimal care pathway. First there is an analysis of the potential and actual referrer network. In the next step information is sent to these referrer network and in the last step there will be an evaluation and an follow-up analysis of the referrer network. The optimization of the allocation is organized by [name] (University Medical Center Hamburg-Eppendorf).

2) **Education and training program for the professionals**

The second implementation intervention concerns the improvement of the professionals' attitudes, knowledge, and skills. The two main components here being the assessment of the current state in all institutions within the clinical centers as well as the development and implementation of an education and training program. The employees of the randomized clinical centers in the intervention group will get a 3-h training. This intervention is organized by [name] (University Hospital Heidelberg, Germany). Due to the Covid-19-pandemic, the training of medical staff is organized as two webinars. The first webinar contains knowledge about risks in mentally ill parents and intervention skills on how to address family-related problems with mentally ill parents or children, respectively. Herewith, a bi-focal perspective is demonstrated i.e., having the needs of parents on the one hand and of children on the other hand in mind when assessing needs and offering support. The second webinar is offered in an interactive format to discuss the content of the first webinar and specific implementation barriers between youth and adult psychiatric services as well as the practice of skills. Changes in attitudes toward working with mentally ill parents will be assessed over three times using the same online survey with the translated family-focused mental health practice questionnaire (26). The contents of the webinar have been published in more detail (27).

3) **Systematic screening**

The third implementation intervention includes a systematic screening process to improve the detection of mentally ill parents with affected children. Employees of the clinical centers fill out two short questionnaires with the parents. This intervention project is organized by [name] (Charité, Berlin, Germany).

The first main question is whether psychiatric patients have responsibility for minors. If this question is answered in the affirmative, parents are presented with two short screening questionnaires of one page each. In the context of the study, sensitivity and specificity will be determined in comparison to standardized instruments (CBCL) and information collected during the family intervention.

The first questionnaire called “Children-Screening” (15) was developed specifically for children of mentally ill parents and piloted in the clinic for child and adolescent psychiatry of Charité. It records in short all potential mental health problems of a child. If the score is above the cut-off, further psychiatric assessment should be made. The second questionnaire called “Family-Screening” (15) was designed as a risk screening and records family risk and protective factors as well as incidences of domestic violence and neglect. The goal is to evaluate support needs for families. The result is presented in a traffic light system (RED-YELLOW-GREEN). RED indicates an urgent need for support. This questionnaire was developed in the child abuse clinic of the Charité and is also piloted there. Both questionnaires are not yet standardized, validated tools.

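### Accuracy of the two screening forms is judged partly against information that only intervention families can supply; if screen-positives are verified more often and this is not corrected, sensitivity is overstated and specificity understated

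*Protocol article*

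**What the plan says.** All statements below are from the protocol article. The section on the three implementation interventions describes the third one, systematic screening. Psychiatric patients are first asked whether they are responsible for minors, and "If this question is answered in the affirmative, parents are presented with two short screening questionnaires of one page each". Of these forms it says that "Both questionnaires are not yet standardized, validated tools". Their accuracy is to be studied: "sensitivity and specificity will be determined in comparison to standardized instruments (CBCL) and information collected during the family intervention".

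The same section says what a result leads to. For the Children-Screening, "If the score is above the cut-off, further psychiatric assessment should be made"; nothing comparable is stated for scores below the cut-off. The Family-Screening "was designed as a risk screening and records family risk and protective factors as well as incidences of domestic violence and neglect" and reports a traffic-light result, of which "RED indicates an urgent need for support".

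On entry to the interventions, the Background says that families in the parent project are screened on family functioning and mental health and then "allocated to different interventions according to his/her indication and the requirements". The Abbreviations describe CHIMPS-P as meant for families who already show problems but have no diagnosis of their own. For inclusion and exclusion criteria the Background refers to the central project's protocol, which is not shown.

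**The concern.** Sensitivity needs the true status of screen-negative as well as screen-positive families, because false negatives are found only among the negatives. The plan names two sources of true status. The CBCL could in principle be completed by any screened parent. Information gathered during a family intervention cannot: a family that enters no intervention has none.

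Entry is by indication, and the article attaches further assessment or support to a high score or a RED result. The natural expectation is that families positive on a form are more likely to have this reference than families negative on it. If accuracy is then computed among families with a reference, missed cases drop out of the denominator of sensitivity, and correctly negative families drop out of the denominator of specificity.

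At stake is the credibility of two forms that are already in use as one of the three implementation interventions. An overstated sensitivity would support wider use of a tool that misses more affected children than reported.

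**Working it through.** The article gives no accuracy figure, verification rate or sample size for the screening evaluation, so there is no stated figure to reproduce. The check concerns the direction and possible size of the bias.

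**Inputs, all assumed for illustration**
- True sensitivity Se = 0.70 and true specificity Sp = 0.80.
- Share of screen-positives verified: vP = 0.80.
- Share of screen-negatives verified: vN, varied from 0.80 down to 0.
- Given the screen result, verification does not depend on true status.

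**Formulas** for accuracy computed among verified families only
- Apparent sensitivity = Se·vP / [Se·vP + (1 − Se)·vN]
- Apparent specificity = Sp·vN / [Sp·vN + (1 − Sp)·vP]

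Prevalence does not enter, because each measure is computed within the truly affected or the truly unaffected.

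**Results**

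| vP | vN | Apparent sensitivity | Apparent specificity |
|---|---|---|---|
| 0.80 | 0.80 | 0.56/(0.56 + 0.24) = 0.70 | 0.64/(0.64 + 0.16) = 0.80 |
| 0.80 | 0.40 | 0.56/(0.56 + 0.12) = 0.82 | 0.32/(0.32 + 0.16) = 0.67 |
| 0.80 | 0.20 | 0.56/(0.56 + 0.06) = 0.90 | 0.16/(0.16 + 0.16) = 0.50 |
| 0.80 | 0.10 | 0.56/(0.56 + 0.03) = 0.95 | 0.08/(0.08 + 0.16) = 0.33 |
| 0.80 | 0 | 0.56/0.56 = 1.00 | 0/0.16 = 0 |
| 0.40 | 0.80 | 0.28/(0.28 + 0.24) = 0.54 | 0.64/(0.64 + 0.08) = 0.89 |

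The first row shows that equal verification leaves both measures unbiased, even though a fifth of families have no reference. The last row shows that the bias reverses if negatives are verified more often. Only vP > vN gives overstated sensitivity with understated specificity. Starting from 0.80/0.80 or 0.80/0.90 gives the same pattern: with vP = 0.80 and vN = 0.20 the apparent values are 0.94/0.50 and 0.94/0.69.

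**What a correction recovers.** Take vN = 0.40 and weight each verified family by the inverse of its verification rate. Among the affected this gives 0.56/0.80 = 0.70 positive and 0.12/0.40 = 0.30 negative, so sensitivity is 0.70/(0.70 + 0.30) = 0.70. Among the unaffected it gives 0.32/0.40 = 0.80 negative and 0.16/0.80 = 0.20 positive, so specificity is 0.80. With vN = 0 the weight for negatives is undefined, and no weighting can recover either measure.

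**The case against.** The strongest reply has four parts.

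*The CBCL is named first.* A reader might infer that screen-negative families have no reference at all. The article does not support that: nothing in it limits the CBCL to intervention families, although nothing says that every screened family completes one. The point therefore applies to part of the reference. That part remains a problem even with a CBCL for all. Intervention families would then be judged on two sources and the rest on one; if either source can establish a case, extra cases would be found mainly where families entered an intervention.

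*The link from the forms to intervention entry is inferred.* The Background does not say that allocation uses these two forms, or that families negative on them get no intervention, and the eligibility rules are in a document that is not shown. This stands. It is why the conclusion is conditional, and why a reader who infers that the bias will certainly occur goes too far. It is also not documented that intervention staff know the screen result, so nothing here rests on that.

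*The article does not say that the CBCL is the reference for the Family-Screening.* One sentence lists two sources for two forms and does not pair them; it may mean the CBCL for the child form and intervention information for the family form. On that reading, though, the Family-Screening rests entirely on the selectively available source.

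*A condensed article may leave such detail elsewhere.* Blinding, how the sources are combined and how missing references are handled may well be set out in a fuller document, and their absence is not criticised. The criticism is of what the sentence does fix: a reference for sensitivity and specificity that includes information tied to intervention entry.

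**Conclusion.** The point holds in conditional form. Part of the stated reference exists only for families who entered an intervention, and the article's own description makes that likely to depend on the screen result. If screen-positives are verified more often and nothing is corrected, sensitivity is overstated and specificity understated. Under the assumed 70%/80% with 80% of positives verified, the distortion is 12 and 13 percentage points when 40% of negatives are verified (82%/67%), and 20 and 30 points when 20% are (90%/50%). It is zero when verification is equal. The rates are assumptions; the article gives none.

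The matter is secondary. Screening accuracy is not among the four listed aims or in H1 or H2, and the randomized comparison of centers is unaffected.

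**What to change.** Amend the sentence on sensitivity and specificity as follows.

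1. For the Children-Screening, make the CBCL the main reference, using all screened families with a CBCL whatever their screen result.
2. Report CBCL completion by screen result, and correct for any difference with the Begg–Greenes method or inverse-probability weighting.
3. Report comparisons of either form with intervention-derived information as descriptive results within intervention families, not as sensitivity and specificity for the screened population. Because indication itself reflects family functioning and mental health, adjusting this source for the screen result alone may not suffice.
4. Do not use the CBCL as accuracy reference for the Family-Screening. The article does not describe the CBCL, but it is generally known as a measure of child problems, whereas this form covers family risk and protection, violence and neglect.

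The change is to the analysis and its wording; no cut-off or clinical rule is touched. The cost is that the reported sensitivity may be lower and less precise, and that the Family-Screening gets no population accuracy figure from these sources. The correction needs some screen-negative families with a CBCL. If there are none, sensitivity and specificity should not be claimed, and obtaining them would need additional data collection.
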